#### Secondary outcomes

The secondary outcomes include the changes in BCVA and CST from baseline to months 1, 3, and 6; assessment of SRF, location and size of cystoid change, continuity of the IS-OS layer, and presence and quantity of HRF in OCT at months 1, 3, 6, and 12; assessment of FAZ, superficial capillary density (sVD), and deep capillary density (dVD) in OCTA at months 3, 6, and 12; re-treatment and diabetic retinopathy (DR) development from baseline to month 12; cost-effectiveness analysis at month 12; and vision-related quality of life (VRQL) at months 6 and 12.

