### OCT

Three-dimensional spectral domain OCT (DRI-OCT Triton, Topcon, Inc, Tokyo, Japan) will be used to acquire all OCT scans. Scanning was centered on the macular fovea with a scan length of 6 mm. The resolution was 5 μm, the scan depth was 4 mm, and the scan mode was horizontal linear scanning of 512 × 128. CST refers to the average thickness of the distance between the retinal pigment epithelium (RPE) and the ILM at the highest point of the retina, which is measured at a circular area surrounding the foveal center with a diameter of 1 mm. Additionally, we will assess SRF, cystoid size (< 100 μm, 100–200 μm, > 200 μm) and location (outer nuclear layer (ONL) or inner nuclear layer (INL)), IS-OS continuity (completely continuous, partly disrupted, or completely disrupted), and presence and quantity of HRF (< 10, 11–20, > 20), vitreomacular interface (detached, vitreomacular adhesion, vitreomacular traction, and epiretinal membrane). The technicians will ensure that the images are centered and of sufficient quality. OCT images will be analyzed and compared preoperatively and at months 1, 3, 6, and 12.

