### Statistical methods

#### Statistical methods for primary and secondary outcomes {20a}

Descriptive statistics will be used to summarize study results and demographic variables. Means and standard deviations will be used to describe the normally distributed data, and medians and interquartile ranges will be used for non-normally distributed data. Categorical variables will be described as percentage and frequency. The two-sample *t*-test or Kruskal–Wallis test will be used to assess continuous variables, while the chi-square test will be used to evaluate categorical variables. A two-sided *p* value of less than 0.05 will be considered statistical significance. Besides, the records of patients with missing data will be deleted to ensure the accuracy of the results. All the data will be analyzed by SPSS 25.0 (Chicago, IL, USA).

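### Three secondary OCT outcomes (cystoid size, HRF quantity, IS-OS continuity) are in ordered classes, but the only test named for categorical variables is a chi-square test that ignores the order

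*Protocol article*

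**What the plan says.** The OCT section of the protocol article sets the classes: "cystoid size (< 100 μm, 100–200 μm, > 200 μm"; "IS-OS continuity (completely continuous, partly disrupted, or completely disrupted"; and "presence and quantity of HRF (< 10, 11–20, > 20". The first and third are bands of a length and a count. The second is an ordered grade with no underlying measurement described. The same section lists SRF, cystoid location (two layers) and the vitreomacular interface (four named states).

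The Secondary outcomes section makes these items outcomes at four visits, for example "continuity of the IS-OS layer, and presence and quantity of HRF in OCT at months 1, 3, 6, and 12".

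The section on statistical methods {20a} has one rule for each type of variable. For categorical variables it says "while the chi-square test will be used to evaluate categorical variables". It does name a rank test, but for the other type: "test or Kruskal–Wallis test will be used to assess continuous variables". The threshold is a two-sided p "value of less than 0.05 will be considered statistical significance". The section on additional analyses {20b} adds regression for adjustment without naming a model. No ordinal or trend method appears anywhere in the article.

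**The concern.** Pearson's chi-square on a 2 × 3 table gives the same result however the three columns are arranged. Swap the middle and worst IS-OS grades and the p value does not change. The test therefore cannot use the fact that one grade is worse than another, and a significant result does not say which arm did better. It also spreads its sensitivity over two degrees of freedom when a treatment effect on these grades would most naturally be a shift in one direction.

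For cystoid size and HRF there is a second, separate loss: a length or count is reduced to three bands before testing. If only the band is stored, no later analysis can recover the value.

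What is at stake is power on named secondary outcomes in a trial planned on 46 evaluable eyes per arm. The article's background section also makes it an aim to find which imaging biomarkers favour surgery over injection.

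The HRF bands have a plain defect of definition as well: below 10, then 11 to 20, so a count of exactly 10 has no class.

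**Working it through.** **1. The plan's own figure.** The only design figure is the BCVA sample size: SD 9.5, margin 5, α 0.05, β 0.2 (Sample size section). Taking α as one-sided and the true difference as 0:

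n = 2 × (1.645 + 0.842)² × 9.5² / 5² = 44.6, so 45 per arm by the normal formula and 46 with the t distribution. The stated 46 is reproduced. Adding 10% gives 46 × 1.10 = 50.6, so 51 per arm, also as stated. I use 46 (evaluable) and 51 (randomised) per arm below.

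The article gives no class frequencies, effects or power for any OCT biomarker. Everything that follows is therefore assumption-based.

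**2. Cost of the extra degree of freedom.** Suppose the whole signal lies in the trend. A 1-df test with 80% power at two-sided 0.05 has noncentrality (1.960 + 0.842)² = 7.85. On 2 df (critical value 5.99) the same noncentrality gives 71% power. Starting from 70% power, (1.960 + 0.524)² = 6.17 gives 60% on 2 df.

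**3. Order lost: ordered three-class item, 46 per arm, simulated.** With a control split of 1/3, 1/3, 1/3 and a common odds ratio of 2.5, the cumulative odds 0.5 and 2 become 1.25 and 5, so the other arm has 0.556, 0.278, 0.167.

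| Control split | Odds ratio | Chi-square | Rank test |
|---|---|---|---|
| 1/3, 1/3, 1/3 | 2.5 | 54% | 65% |
| 1/3, 1/3, 1/3 | 3 | 70% | 79% |
| 50/30/20 | 2.5 | 47% | 58% |

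**4. Both losses: normal variable shifted between arms, then cut into three classes** at five pairs of control-arm percentiles (20,000 trials per cell). Results for tertile cuts at 46 per arm:

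| Shift (SD) | t-test, uncut | Wilcoxon, classes | Chi-square, classes |
|---|---|---|---|
| 0.3 | 28.9% | 24.2% | 18.5% |
| 0.5 | 65.5% | 55.0% | 45.0% |
| 0.8 | 96.6% | 91.0% | 85.3% |

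Over all five cut pairs, shifts of 0.3 to 0.8 SD and both sample sizes:

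- Wilcoxon on classes minus chi-square: 4 to 11 points (5 to 11 at 46 per arm alone).
- t-test on uncut values minus chi-square: 8 to 26 points (10 to 26 at 46 per arm alone).

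With no shift, every test rejected in 4.6% to 5.3% of trials.

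**5. The gap at 10.** This needs no model: 10 is neither below 10 nor within 11 to 20. As an illustration only, take a negative binomial count with k = 2. At mean 15, P(10) = 11 × (2/17)² × (15/17)¹⁰ = 0.044. At mean 10, P(10) = 11 × (2/12)² × (10/12)¹⁰ = 0.049. So roughly 4% to 5% of eyes would have no class under that assumption.

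**The case against.** The statistical section is a general rule in a condensed article. It does not name these three outcomes, and an analysis plan that is not shown could choose an ordinal test for each. The regression in {20b} is not ruled out as an ordinal model. The outcomes are secondary and no power is claimed for them. The chi-square test is valid, direction can be read from the promised frequencies, and a general test is more sensitive if the arms differ in a non-monotone way.

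Most of this stands, and it limits the weight of the point. It does not remove it. The article is not silent: it names a test for categorical variables, reserves its rank test for continuous ones, and leaves its regression model undefined. The bands and the gap at 10 are fixed at the data-capture stage, where an analysis plan may come too late.

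Several stronger readings are tempting but unsupported:

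- *That all OCT biomarkers are affected.* SRF, cystoid location and the vitreomacular interface are not three ordered classes, and chi-square suits them. CST stays continuous.
- *That the plan loses a fixed amount, say 10 to 17 points.* No effect is stated, and such a figure merges two different losses. For IS-OS continuity only the loss of order can apply.
- *That graders already hold an exact count or size, so recording it is free.* The OCT section does not say whether they measure or simply assign a band.
- *That the cut points are faulty because no guideline is cited for them.* An article need not cite one for imaging grades.

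**Conclusion.** The point holds for cystoid size, HRF quantity and IS-OS continuity, and only for these. The stated test ignores the order of their classes although a better test is available at almost no cost. Under assumed monotone shifts with 46 to 51 eyes per arm, the loss is about 4 to 11 points of power from ignoring order. For the two outcomes with an underlying size or count, the total is about 8 to 26 points when banding is included. Both ranges rest on an assumed normal shift of 0.3 to 0.8 SD and assumed cut positions, not on figures in the article. With a non-monotone difference chi-square need not lose power at all.

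A reader might infer that the trial's conclusion is at risk. It is not: type I error stays near 5%, and the BCVA and CST comparisons are untouched. The gap at an HRF count of 10 is a certain, small error of definition.

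**What to change.** In the statistical methods section {20a}, state that ordered classes are compared with a Wilcoxon/Mann-Whitney or linear trend test, or with a proportional-odds model adjusted for the baseline grade. Keep chi-square for nominal items: SRF present or absent, cystoid location, vitreomacular interface.

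In the OCT section, close the HRF gap, for example ≤ 10, 11–20, > 20. Where the grader obtains the HRF count or the cystoid size in μm, record it, analyse it on that scale and keep the bands for description.

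The cost is mainly wording, plus slightly more data entry. If graders at present only assign a band, recording values would also change the grading step, and the sponsor should decide whether that is worthwhile. The order-respecting tests are less sensitive to non-monotone differences, and the proportional-odds model brings its own assumption. No patients or visits are added, and the article says that recruitment had not begun at this version.

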### Criteria for discontinuing or modifying allocated interventions {11b}

If serious adverse events occur or are likely to occur that severely impact vision (such as endophthalmitis, retinal damage, etc.), or if patients are unable to tolerate the intervention due to their physical condition, the intervention will be terminated or modified. The patients will withdraw from the study and receive appropriate treatment measures.

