### Outcomes {12}

#### Primary outcome

The primary outcome is the changes in BCVA and CST from baseline to month 12 between the two groups.

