### Sample size {14}

The sample size is estimated by the change of BCVA using PASS 15.0 (PASS 15.0.5 NCSS, LLC, USA). According to a published paper [9], mean BCVA change of IVC from baseline to month 12 was 8.2 ± 9.5 ETDRS letters. The maximum difference of 5 ETDRS letters was chosen for non-inferiority margin between groups. The sample size was calculated based on α level of 0.05 and *β* level of 0.2, N1 = N2 = 46. Then, the ultimate sample size is 102 (51 of each group) assuming a 10% dropout rate.

The non-inferiority margin was chosen because 5 ETDRS letters is considered clinical insignificant in practice. And the sample size is also sufficient for analysis of the change of CST based on previous studies [9, 36] (364 ± 88.6 μm and 200 ± 210 μm for IVC and vitrectomy combined with ILM peeling respectively).

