### OCTA

OCTA images will be obtained following a standard protocol with the AngioVue OCTA system (RTVue-XR Avanti, Optovue, Fremont, California, USA). The scanning area, centered on the fovea, was captured in 3 × 3 mm sections with a resolution of 304 × 304 pixels. The in-built RTVue XR Avanti AngioVue software will help reveal FAZ, sVD, and dVD through the automated layer segmentation. Motion artifacts, a weak signal (5/10), poorly focused scans, or segmentation failure will all result in poor image quality, which will be disregarded. OCTA images will be analyzed and compared preoperatively and at months 3, 6, and 12.

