### Methods in analysis to handle protocol non-adherence and any statistical methods to handle missing data {20c}

Missing data will be managed using a combination of the last observation carried forward (LOCF) and multiple imputation (MI) methods. Sensitivity analyses will also be performed to assess the impact of different imputation methods on study results.

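### The article both deletes and imputes patients with missing data, and does not say which rule governs the primary month-12 analysis

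*Protocol article*

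**What the plan says.** The protocol article gives two rules for missing data.

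- Statistical methods for primary and secondary outcomes {20a}: "the records of patients with missing data will be deleted to ensure the accuracy of the results".
- Methods to handle protocol non-adherence and missing data {20c}: "Missing data will be managed using a combination of the last observation carried forward (LOCF) and multiple imputation (MI) methods". It adds: "Sensitivity analyses will also be performed to assess the impact of different imputation methods on study results".

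Neither section refers to the other, restricts its rule to particular outcomes, or calls itself primary or supportive. Section {20c} does not say how LOCF and multiple imputation are to be combined.

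Three other places bear on the point. The primary outcome section reads: "The primary outcome is the changes in BCVA and CST from baseline to month 12 between the two groups". Section {11b}, on patients with serious vision-threatening events or who cannot tolerate the intervention, says: "The patients will withdraw from the study and receive appropriate treatment measures". The sample size section {14} plans for loss: "the ultimate sample size is 102 (51 of each group) assuming a 10% dropout rate".

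**The concern.** The two rules define different analysis sets. Under {20a} a patient without month-12 data leaves the comparison. Under {20c} the same patient stays, with an imputed value. Two analysts could each follow the article faithfully and test different patients, and the choice could be made after results are known. This is more than detail left to an analysis plan, because a plan that follows one section must contradict the other.

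The choice matters because missingness here may not be neutral. One arm has surgery and the other has injections, participants and surgeons are not masked, and {11b} links withdrawal to serious ocular events. If the eyes that do badly after PPV are the ones removed, the retained PPV mean is too high. In a non-inferiority trial that error runs towards declaring success.

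LOCF has a weakness of its own. It assumes that nothing changes after the last visit, although PRN conbercept, PRP and cataract surgery are all allowed up to month 12. Its bias can run in either direction.

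**Working it through.** **1. Can the two rules coexist?** They could if deletion were the sensitivity analysis, or if each rule covered different outcomes. The sensitivity analyses in {20c} compare imputation methods, and deletion is not one. Section {20a} is headed as covering primary and secondary outcomes, and {20c} is not limited to any outcome. The text offers no reconciliation.

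**2. Reproducing the planned sample size.** Inputs from {14}: SD 9.5 letters ("mean BCVA change of IVC from baseline to month 12 was 8.2 ± 9.5 ETDRS letters"), margin 5, α 0.05, β 0.2. I take the true difference as 0.

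- Normal formula, one-sided 0.05: n = 2 × 9.5² × (1.645 + 0.842)² / 5² = 44.6, so 45 per arm.
- Noncentral t, one-sided 0.05: 46 per arm, power 80.5%. This matches the article.
- One-sided 0.025 gives 57 (normal) or 58 (t), which does not match. Section {20a} sets a two-sided 0.05 level, so both levels are shown below.
- Dropout: 46 × 1.10 = 50.6, so 51 per arm and 102 in total, as stated.

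**3. Patients analysed at the planned 10% dropout.** Imputation keeps 102. Deletion keeps 102 × 0.9 = 91.8, about 46 per arm.

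**4. Bias from deletion.** Let a share w of the PPV arm be deleted, and let those patients average D letters worse than those retained, with no such effect in control. The full-arm mean equals the retained mean minus w × D, so deletion moves the difference by w × D towards non-inferiority. The article gives neither w nor D. I assume w = 5–15% and D = 5–20 letters.

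- Smallest: 0.05 × 5 = 0.25 letters.
- Middle: 0.10 × 10 = 1.0 letter, or 20% of the margin.
- Largest: 0.15 × 20 = 3.0 letters, or 60% of the margin.

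**5. Effect on the error rate.** Take a true difference of −5 among all randomised patients, SD 9.5 and 46 analysed per arm. The standard error is 9.5 × √(2/46) = 1.98. The noncentral t with noncentrality shift/1.98 and 90 degrees of freedom gives the chance of falsely declaring non-inferiority:

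| Shift (letters) | One-sided 0.05 | One-sided 0.025 |
|---|---|---|
| 0 | 5.0% | 2.5% |
| 0.25 | 6.4% | 3.3% |
| 1.0 | 12.6% | 7.2% |
| 1.5 | 18.6% | 11.3% |
| 3.0 | 44% | 32% |

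The number per arm is held at 46 throughout for simplicity.

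**6. Bias from LOCF.** The bias is roughly the excess early dropout in one arm times the gap between the last value and month 12. Assuming 5–10% excess and a gap of 2–8.2 letters (the upper end being the whole control-arm gain in {14}), it runs from 0.05 × 2 = 0.1 to 0.10 × 8.2 = 0.82 letters, in either direction.

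**The case against.** The textual conflict is hard to dispute. The fair objections concern what a reader might build on it.

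- **Lost power.** A reader might infer that deleting dropouts leaves the trial underpowered. It does not at the planned rate: the allowance in {14} exists for this, and 46 per arm with 80.5% power remain. The issue is bias and pre-specification.
- **One bad OCTA scan removes the patient.** The OCTA section says of poor scans that "segmentation failure will all result in poor image quality, which will be disregarded". Joined to {20a} at its most literal, this would delete the patient's BCVA too. But the OCTA section discards images and says nothing of patients, and {20a} can equally be read as deletion analysis by analysis. Any figure also needs a failure rate that the article does not give. With 10% dropout and three OCTA visits, 10% independent failure per visit leaves 102 × 0.9 × 0.9³ = 66.9 patients (33 per arm; power 68% or 56% at the two levels). At 5% it is 102 × 0.9 × 0.95³ = 78.7 (39 per arm; 74% or 63%). If the same 10% of eyes fail each time, it is 102 × 0.9 × 0.9 = 82.6 (41 per arm; 76% or 65%). Clear media for adequate imaging is an inclusion criterion. This range shows loose wording and is no forecast.
- **The bias is assumed.** This stands. The article fixes neither its size nor its direction. That the two rules would give opposite conclusions is possible, but not shown.
- **LOCF does not stand alone.** It is paired with multiple imputation, with sensitivity analyses promised, and its illustrated bias stays below 1 letter. It is the lesser issue.

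**Conclusion.** The conflict is real in the current text and has to be resolved. Section {20a} deletes, {20c} imputes, and nothing says which governs month-12 BCVA and CST. Deletion gives an unbiased comparison only if missingness is unrelated to outcome within each arm, and {11b} makes that doubtful.

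On the assumed range, deletion shifts the BCVA difference by 0.25–3.0 letters against a margin of 5. A 1.0-letter shift raises false non-inferiority from 5% to about 13%, or from 2.5% to about 7%. These figures depend on outcome-related loss in the PPV arm only, an SD of 9.5 in both arms and 46 analysed per arm. They show what is at stake and do not predict this trial's result. The documents do not support a claim that the trial is underpowered by the planned dropout, or that it will be biased by a known amount.

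**What to change.** 1. Remove the deletion sentence from {20a}.
2. In {20c}, name one primary method for both month-12 BCVA and month-12 CST, with patients analysed as randomised. Multiple imputation is already named there and could use arm, baseline and the month 1, 3 and 6 values. A repeated-measures model over the same visits is an equally good choice, but the text should then say how patients with no post-baseline value are handled, since they contribute little to such a model. Test the month-12 BCVA contrast against −5.
3. Keep complete-case analysis and LOCF at most as labelled sensitivity analyses.
4. Add a delta-adjusted multiple imputation that makes missing PPV outcomes progressively worse, and report the point at which non-inferiority is lost. This addresses withdrawal after serious events directly, which standard imputation from earlier visits may not.
5. State that missing OCT and OCTA data are handled outcome by outcome, so that a discarded image does not affect BCVA.

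The cost is a wording change and a little more analysis. BCVA and OCT are already scheduled at months 1, 3, 6 and 12 in Table 1, so no new data are needed. The choice should be recorded before outcomes are examined by arm.

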### Interim analyses {21b}

The research committee of Tianjin Medical University Eye Hospital will evaluate the progress and safety of the study in the interim. Final decision regarding the termination of the trial will be made jointly by the principal investigator and the regulatory body overseeing the study. They will base their decision on the results of the interim analyses, safety data, and efficacy data as well as ethical and legal requirements.

### Methods for additional analyses (e.g., subgroup analyses) {20b}

Regression analysis will be used for adjusted analysis to control for confounding factors.

### Methods in analysis to handle protocol non-adherence and any statistical methods to handle missing data {20c}

Missing data will be managed using a combination of the last observation carried forward (LOCF) and multiple imputation (MI) methods. Sensitivity analyses will also be performed to assess the impact of different imputation methods on study results.

### Plans to give access to the full protocol, participant-level data, and statistical code {31c}

Access to the full protocol and participant level-data can be acquired on ClinicalTrials.gov.

### Oversight and monitoring

#### Composition of the coordinating center and trial steering committee {5d}

The research committee of Tianjin Medical University Eye Hospital will meet regularly to review the progress of the research, make important decisions, and ensure that the trial adheres to ethical and regulatory standards.

### Composition of the data monitoring committee, its role and reporting structure {21a}

The data monitoring committee comprises two independent statisticians and one independent clinician. They will review the accumulating data every quarter to assess the progress of the study, make important decisions regarding participant safety, and evaluate the integrity of this trial.

